## Abstract

**Background:**

Neurogenic detrusor overactivity (NDO) is a serious and common complication after spinal cord injury, affecting patients’ quality of life seriously. Therefore, we developed this research protocol to evaluate the efficacy of repetitive functional magnetic stimulation (rFMS) in the sacral nerve in patients with neurogenic detrusor overactivity (NDO) after suprasacral spinal cord injury (SCI) and provide more options for rFMS in treating NDO after suprasacral SCI.

**Methods:**

This study is a single-center, randomized, parallel-group clinical trial. We will recruit the patients with NDO after suprasacral SCI in the Rehabilitation Department of the Affiliated Hospital of Southwest Medical University from September 2022 to August 2023. They will be assigned to the rFMS group and the sham stimulation group randomly. The sample size is 66, with 33 patients in each group. The rFMS group will receive real rFMS treatment of the sacral nerve (100% stimulation intensity, 5 Hz, 20 min each time, five times a week), and the sham group will receive sham stimulation. Both groups will receive similar treatment strategies, including medication, standard urine management, acupuncture treatment, and health education. The bladder compliance (bladder capacity/detrusor pressure) and pudendal nerve electromyography will be evaluated at baseline, 8th week of treatment. The residual volume of the bladder and bladder diary will be recorded once a week during 8 weeks of treatments. SCI-QOL and NBSS will be evaluated at baseline, the 4th and 8th week of treatment. In addition, the above assessments will be followed up at 8 weeks after the end of treatment.

**Discussion:**

It is expected that the bladder function, symptoms, and quality of life might be significantly improved after rFMS of the sacral nerve.

**Trial registration:**

The China Clinical Trials Registry has approved this study, registration number: ChiCTR2100045148. Registered on April 7, 2021.

**Supplementary Information:**

The online version contains supplementary material available at 10.1186/s13063-023-07207-1.

## Administrative information

Note: the numbers in curly brackets in this protocol refer to SPIRIT checklist item numbers. The order of the items has been modified to group similar items (see http://www.equator-network.org/reporting-guidelines/spirit-2013-statement-defining-standard-protocol-items-for-clinical-trials/).

## Introduction

### Background and rationale {6a}

Neurogenic detrusor overactivity (NDO) is recognized when detrusor overactivity accompanies a relevant neurological condition [1]. As a type of neurogenic bladder (NB), NDO is quite common in patients with suprasacral spinal cord injury (SCI). NDO can lead to intermittent increases in intravesical pressure and urine leakage [2]. Untreated NDO can lead to many complications, such as recurrent urinary tract infections, urinary calculi, and urethral strictures, which seriously affect the patient’s quality of life [3]. Currently, interventions for NDO include medicine, acupuncture, sacral neuromodulation, peripheral tibial nerve stimulation, pelvic floor muscle function training, and surgical intervention [4–6]. Functional magnetic stimulation (FMS) is a non-invasive treatment for NDO that has emerged in recent years. Investigators have observed a well-tolerated treatment of stress urinary incontinence with no pain or side effects by placing the therapeutic coils flatly on the sacrum (S2–S4), resulting in an electromagnetic impact [7]. Previous studies have shown that magnetic stimulation might effectively treat NB [5, 8, 9]. However, these articles were observational studies or small sample studies. There is a lack of high-quality research on repetitive functional magnetic stimulation (rFMS) of sacral nerves in the treatment of NDO secondary to suprasacral SCI. Therefore, we developed this research to evaluate the efficacy of rFMS in the sacral nerve in patients with NDO after suprasacral SCI and provide more options for rFMS in treating NDO.

### Objectives {7}

To evaluate the efficacy of repetitive functional magnetic stimulation (rFMS) in the sacral nerve in patients with neurogenic detrusor overactivity (NDO) after suprasacral spinal cord injury (SCI)To provide more options for rFMS in treating NDO after suprasacral SCI.

### Trial design {8}

This study will be a double-blind, randomized controlled trial. Patients who fulfill the inclusion criteria and sign the informed consent form will be randomly divided into the rFMS group and sham rFMS group (sham group) in a 1:1 ratio. Assessments are made before treatment, during 8 weeks treatment, and 8 weeks after treatment (Fig. 1). The purpose of this study is to design a high-quality randomized controlled trial and realize the complete randomization of participants. The patients, professional evaluators, and data analysts are all blinded, so as to provide reliable data for the recovery of bladder function of suprasacral SCI with NDO after rFMS treatment.

**Fig. 1 Fig1:**
[figure not shown]
Summary of study protocol

## Methods: participants, interventions, and outcomes

### Study setting {9}

All the patients will come from the Rehabilitation Medicine Department, the Affiliated Hospital of Southwest Medical University. Patients are considered for inclusion if they meet the criteria as defined below.

### Eligibility criteria {10}

The inclusion criteria are as follows: ① definitely diagnosed as suprasacral SCI [10], the course of the disease is more than one month; ② age: 18–60 years old; ③ urodynamics indicates NDO [11]. The exclusion criteria are as follows: ① patients with metal implants in the lumbosacral area; ② patients with cognitive dysfunction who cannot cooperate; ③ patients with unstable vital signs; ④ those who have a history of botulinum toxin injection within 6 months or a history of bladder/sphincter surgery; ⑤ patients with unstable fractures who cannot complete urodynamics. Once patients are enrolled, we will use questionnaires to record participants’ baseline data such as age, gender, symptoms, duration, past treatments (including medications and rehabilitation), and more.

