## Assignment of interventions: allocation

### Sequence generation {16a}

The random allocation table will be generated by SPSS 23.0 software, and the included cases will be randomly divided into treatment and control groups. The research coordinator is responsible for randomization, which will be carried out by simple 1: 1 draw (for each pair of patients who are recruited).

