## Statistical methods

### Statistical methods for primary and secondary outcomes {20a}

We will use SPSS 23.0 statistical software for data analysis with a statistical significance level set at* p* ≤ 0.05. We will apply the chi-square test or Fisher’s exact test to analyze categorical data such as symptoms or gender. Data that is not normally distributed will be analyzed using nonparametric analysis. In addition, repeated measures ANOVA and post hoc tests will be used to analyze statistically significant differences between and within the groups.

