### Methods for additional analyses (e.g., subgroup analyses) {20b}

No additional analyses are planned.

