The changes in pudendal innervation are closely related to NB filling symptoms and detrusor overactivity [39]. There are two different pathological mechanisms of NDO secondary to SCI: increased afferent signaling and abnormal handling of efferent activity [28]. The high center lost its inhibitory effect on the low center after suprasacral SCI. Suprasacral SCI releases the spinal cord segmental micturition reflex from supraspinal modulation and increases the injury-induced release of bladder neurotrophic factors such as brain-derived neurotrophic factor, glial‐derived neurotrophic factor, and ciliary neurotrophic factor. These neurotrophic factors promote Na + channel activation and K + channel deactivation, which subsequently increase the hyperexcitability of the dorsal root ganglion neurons innervating the urinary bladder and activate hypermechanosensitive C‐fiber bladder wall afferents [40–42]. rFMS of the sacral nerve can improve NDO symptoms by different pathways. The excitatory impulses produced by magnetic stimulation ascending to the thoracolumbar sympathetic neurons can excite the sympathetic nerve and inhibit the parasympathetic nerve, thus decreasing detrusor pressure [43]. Stimulation of the sacral nerve might induce an interneuronal change in the spinal reflex arc or spinobulbospinal reflex arc to inhibit the activity of the dominant C-fibers in neurological injury [44]. Therefore, it is meaningful to record pudendal nerve evoked potentials. At present, many studies have used urodynamics or electrophysiological examination of the pudendal nerve to evaluate sacral nerve implantation electrodes for regulating the NB [45–48]. This is a clinical trial, and we will not explore its specific mechanism further. But we will also measure the pudendal nerve evoked potential as one of the outcomes. At the same time, NDO will seriously affect patients’ quality of life. Therefore, we will use subjective assessments (bladder diary, SCI-QOL questionnaire, NBSS) and objective assessments (urodynamics, pudendal nerve electromyography) to evaluate the efficacy of sacral nerve rFMS in the treatment of NDO after SCI.

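### Time since injury ranges without limit from one month and is recorded at baseline, but is used neither in the allocation nor in the stated analysis; this costs precision, not validity of the between-group test.

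*Protocol article*

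**What the plan says.** - **Entry** (Eligibility criteria {10}): a diagnosis of suprasacral SCI where "the course of the disease is more than one month". No upper limit is given. Urodynamic evidence of NDO is also required.
- **Baseline data** (same section): a questionnaire will "record participants’ baseline data such as age, gender, symptoms, duration, past treatments (including medications and rehabilitation), and more". Duration is therefore collected from everyone.
- **Allocation** (Trial design {8}; Sequence generation {16a}): patients are "randomly divided into the rFMS group and sham rFMS group (sham group) in a 1:1 ratio", and the randomisation is "carried out by simple 1: 1 draw (for each pair of patients who are recruited". No stratification factor is named.
- **Analysis** (Statistical methods {20a}): "repeated measures ANOVA and post hoc tests will be used to analyze statistically significant differences between and within the groups". No covariate is named and none is excluded. Under {20b}, whose heading gives subgroup analyses as its example: "No additional analyses are planned".
- **Biology** (Discussion): suprasacral SCI, among other effects, "increases the injury-induced release of bladder neurotrophic factors". No time course is attached to this.
- **Follow-up**: 8 weeks of treatment and 8 weeks afterwards, with compliance measured at baseline, week 8 and the end of follow-up.

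**The concern.** A patient enrolled five weeks after injury is followed for 16 weeks, about three times the interval since injury (16/5 = 3.2). For someone injured ten years ago the same 16 weeks are negligible. If the bladder is still changing in the first patient and stable in the second, part of the spread in compliance change is explained by time since injury. Left out of the model, that part stays in the error term. In a small trial the arms may also differ by chance in their share of early patients, which moves the estimate in that one trial. The variable that would deal with both is already on the baseline questionnaire, but the article gives it no role.

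**Working it through.** **Inputs from the article (Sample size {14}).** Difference 8, SD 9 ml/cmH2O, type I error 5% (two-sided assumed), power 90%, 26 evaluable and 33 recruited per arm.

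**Assumptions, not in the article.** Early share p = 0.4 (26 of 66 patients). The gap D in 8-week spontaneous change between early and late patients is 4 to 10 ml/cmH2O.

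**1. The plan's own figure.** n = 2 × SD² × (1.960 + 1.282)² / difference² = 2 × 81 × 10.51 / 64 = 26.6, so 27 against the stated 26. Dropout: 26 / 0.8 = 32.5, so 33. The plan's number follows from 8 and 9. (The standardised effect of 0.25 in the same section does not match 8/9 = 0.89; that is a separate matter.) A t-test with 26 per arm has power 88.2% for a difference of 8 and 50.2% for 5.

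**2. Bias and type I error.** Simulated trials with 26 per arm, half of patients early, D = 4, 8 or 12, and an unadjusted t-test:

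| True difference | Mean estimate | Rejection rate when the true difference is 0 |
|---|---|---|
| 0 | −0.02 to 0.02 | 4.7% to 5.2% |
| 8 | 8.00 to 8.04 | – |

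Leaving the factor out causes no systematic error between arms.

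**3. Chance imbalance.** With 26 early patients among 66 and 33 per arm (hypergeometric, which treats the paired draw as a random split), the early share differs between arms by at least 15 points in 20.7% of trials and by at least 20 points in 7.7%. Shift at 15 points: 0.15 × 4 = 0.6 and 0.15 × 10 = 1.5 ml/cmH2O, or 8% to 19% of 8. The standard error of the difference is 9 × √(2/26) = 2.50, so the shift is 0.24 to 0.60 standard errors.

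**4. Precision, if the SD of 9 already contains this variation.** Variance explained = p(1 − p)D² / 81; residual SD = √(81 − 0.24 D²).

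| D | Share of variance | Residual SD | Power for 8 | Power for 5 |
|---|---|---|---|---|
| No adjustment | – | 9.00 | 88.2% | 50.2% |
| 4 | 3.84/81 = 4.7% | 8.78 | 89.6% | 52.1% |
| 10 | 24/81 = 29.6% | 7.55 | 96.3% | 64.9% |

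**5. Precision, if the variation comes on top of SD 9.** The total SD is √(81 + 3.84) = 9.21 or √(81 + 24) = 10.25. Unadjusted power for 8 is then 86.7% or 78.8%. Adjustment brings the residual SD back to 9, and power to about 88%.

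**6. Within-group tests.** Assume early patients improve spontaneously by D, late patients by 0, and the SD of change is 9. With no rFMS effect at all, mean change in one arm is 0.4 × 4 = 1.6 or 0.4 × 10 = 4.0. A one-sample t-test on 26 patients is then significant in about 14% or 59% of trials.

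**The case against.** The strongest reply is that the sham arm settles the matter. Both arms receive the same background care, natural course acts on both, and randomisation balances duration in expectation. Step 2 bears this out. A reader might infer that natural recovery could mimic an rFMS effect between groups, or that duration is not balanced at all; the documents do not support either. Chance imbalance and inflated error are also not two separate harms, since both are sampling error that the standard error already carries.

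Three further replies stand. The article lists no model terms, so it cannot be said to restrict the ANOVA to group and time, and the statement on additional analyses does not bar a covariate in the main model. An unseen analysis plan may name one. Next, the Discussion describes a mechanism but no time course, so continuing change at five weeks is an inference; and since every patient must already show NDO, the range of bladder states may be narrower than the range of durations suggests. Finally, the upper assumed gap of 10 exceeds the whole planned difference of 8.

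What does not fall is the factual core. The range is open-ended, the variable is collected, the allocation leaves it out, and no use in the analysis is stated. The planned within-group tests have no sham comparison to remove natural course, and a covariate would not give them one.

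**Conclusion.** The point holds as one of precision and of robustness to chance imbalance. It is not a point of bias. Under the assumed 40% early share and a 4 to 10 ml/cmH2O gap within the SD of 9, adjustment raises power at 26 per arm from 88% to 90–96% for a difference of 8. If the variation is additional to the SD of 9, unadjusted power is about 79–87%, below the planned 90%. At the low end the gain is one or two percentage points, and nothing in the article shows where in the range the truth lies. The separate caution on within-group change does not depend on the exact size: if patients change spontaneously, such tests cannot separate that from treatment.

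**What to change.** Before unblinding, pre-specify time since injury as a covariate in the between-group week-8 comparison of bladder compliance, in one fixed form such as log time. State that conclusions rest on this contrast and that within-group changes are descriptive.

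The cost is one degree of freedom and no new data, since duration is already recorded. If it turns out not to be prognostic, little is lost.

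Separate early and late treatment estimates, if shown, should be labelled descriptive. With 40% early there would be about 0.4 × 26 ≈ 10 evaluable early patients per arm. The 95% half-width is 2.10 × SD × √(2/10), about 7.1 to 8.5 ml/cmH2O for SDs of 7.55 to 9, which is about as wide as the target effect itself.

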### Who will take informed consent? {26a}

Patients with NDO will be screened for eligibility to participate in this study based on the abovementioned criteria. patients assessed as qualified by the treatment group are invited to meet with the research physician to discuss any remaining questions and sign the informed consent.

### Additional consent provisions for collection and use of participant data and biological specimens {26b}

In the consent form, participants will be asked if they agree to use of their data when they choose to withdraw from the trial. Participants will also be asked for permission for the research team to share relevant data with people from the Universities taking part in the research or from regulatory authorities, where relevant. This trial does not involve collecting biological specimens for storage.

## Interventions

### Explanation for the choice of comparators {6b}

The sham group will receive sham rFMS stimulation and medication, standard urine management, acupuncture treatment, and health education.

### Intervention description {11a}

The rFMS group will receive real rFMS treatment of the sacral nerve, while the sham group will receive sham stimulation. Both groups will receive similar treatment strategies, including medication, standard urine management, acupuncture treatment, and health education.

#### rFMS and sham stimulation

All magnetic stimulation treatments will be performed by an experienced rehabilitation therapist specializing in neurorehabilitation for over 5 years. For the rFMS group, the patient takes the prone position and aligns the centers of the two circular magnetic coils with the third sacral nerve (S3) holes on both sides (the upper edge of the sacrum and the midpoint of the coccyx connect one lateral finger on the left and right sides). For the first treatment, motor thresholds will be measured with single-pulse stimulation. The parameters of rFMS treatment will be as follows: the stimulation intensity will be 100%; the frequency will be 5 Hz; 20 min each time, five times a week, for 8 consecutive weeks. Simultaneously, the sham group will use a sham coil, which will not generate a magnetic field but has a similar appearance and sound during operation. The frequency and treatment time will be the same as in the rFMS group, except that the coil does not generate a magnetic field.

#### Medication

According to relevant guidelines [12], each patient will receive tolterodine with a dose of 2 mg twice a day.

#### Bladder management strategy

For bladder emptying, the individualized management strategy is selected according to the patient’s condition, mainly including indwelling catheterization and intermittent catheterization, with the frequency determined according to residual urine.

#### Acupuncture treatment

Acupuncture treatment will be performed by an experienced traditional Chinese medicine doctor who has been in acupuncture for more than 5 years. Select Tianshu, Guanyuan, Qihai, Sanyinjiao, Yinlingquan, and other acupoints to clean and disinfect each point; then acupuncture the acupoints, and leave the needle for 30 min. The acupuncture will be conducted once a day, five times a week, for 8 weeks.

### Criteria for discontinuing or modifying allocated interventions {11b}

There will be no pre-defined criteria for stopping or modifying the allocated intervention. Participation is voluntary. Participants may withdraw from the voluntary trial at any time for any specific reason. Withdrawal from participation has no negative consequences or adverse effects on participants. Researchers may also terminate participation if serious adverse events occur during the intervention. We will suggest that patients who withdraw from the trial continue to standardize the treatment of NDO, so that their subsequent normal medical care will not be affected.

### Strategies to improve adherence to interventions {11c}

Encourage adherence to treatment through weekly evaluations and psychological intervention by experienced psychologists when necessary. Strategies may include encouragement and setting specific goals and dates for weekly physical and drug therapy. The whole process of rFMS treatment will be supervised by an experienced rehabilitation therapist specializing in neurorehabilitation in our center.

### Relevant concomitant care permitted or prohibited during the trial {11d}

All participants will receive medication, standard urine management, acupuncture treatment, and health education. Health education is an organized, planned, and implemented educational activity. It assists individuals and groups in acquiring knowledge about health care, establishing health ideas, and voluntarily embracing educational activities supportive of healthy habits and lifestyles through information dissemination and behavioral intervention. Health education about NDO includes the rationale for bladder emptying options, drinking water plans, prevention of urinary tract infections, etc.

### Provisions for post-trial care {30}

In the event of study-related damage or injuries, the Affiliated Hospital of Southwest Medical University shall provide free symptomatic treatment. If the injury is serious, invite relevant experts for treatment and provide medical compensation.

### Outcomes {12}

#### Primary outcome

The primary outcome is the bladder compliance measured by urodynamic testing. Bladder compliance is the relationship between a change in bladder capacity and a change in detrusor pressure (Pdet) [13]. Urodynamic examinations will be performed by the same experienced technician who has been performing urodynamic examinations for more than 5 years. The detection steps are as follows: ① The day before the examination, the patient is given a glycerin enema to clear up dry stools. The skin around the anus and perineum is prepared, and pubic hair is removed if necessary. ② On the day of the examination, the patient is placed in a supine position, the genital area is routinely disinfected, sterile towels are applied, and a 6F double-lumen manometry catheter is inserted into the bladder through the urethra and will be fixed with tape (penis for males, perineal for females). Insert an 8F balloon catheter into the rectum, inject an appropriate amount of fluid into the balloon of the rectal catheter, and place it in the patient’s rectum to a depth of about 10 cm. ③ During the measurement, the patient will take the lithotomy position. And the normal saline will fill the bladder with a perfusion rate of 50 ml/min by using a water pump. The patient will be told to cough before the start of perfusion to suppress the urge to urinate during perfusion, to cough again before the end of the assay, and to report when the patient feels the first urge to urinate and feels that the maximum cystometry volume been reached. Measure and record using the sensor-related indicators. ④ Obtain bladder compliance, abdominal pressure (Pabd), intravesical pressure (Pves), Pdet, urine flow rate (Q), and other indicators. Safe bladder capacity refers to the bladder capacity when the bladder pressure reaches 40 cmH_2_O or occurring urine leakage in the filling period [14]. And the Pdet will be measured in the urodynamic tests described above.

